### Statistical analysis

All analyses will be performed according to the intention-to-treat principle, that is, all randomized patients will be analysed in the groups to which they were originally allocated and will be blinded to treatment assignment. Baseline patient characteristics will be compared and described using the appropriate statistics. Categorical variables will be presented as the numbers and percentages and will be analyzed by the *χ*^2^- tests or Fisher’s exact tests, or when appropriate, as relative risks. Continuous variables will be checked for normal distribution by the Kolmogorov-Smirnov test. Normally distributed variables will be expressed by their mean and standard deviation; non-normally distributed variables will be expressed by their medians and 95% confidence levels. Comparisons of continuous variables will be performed using Student’s *t*-test for normally distributed variables and the Mann-Whitney U test for non-normally distributed variables. Appropriate (linear, logistic, or Poisson) regression will be generated for the identification of the determinants of outcomes and for the correction of baseline covariates.

One-way repeated measures analysis of variance (ANOVA) were used to determine differences in the sleep variables, the subjective sleep quality, anxiety levels and plasma levels of melatonin, cortisol and norepinephrine. Twenty-eight day mortality will be analysed according to the Kaplan-Meier method and the results will be compared with the log-rank test hazard ratios and reported with 95% confidence limits. The number of delirium-free days, ventilation-free days and antibiotics-free days will be tested by Student’s *t*-test for normally distributed data and the Mann-Whitney U-test for non-normally distributed data. The differences in adverse events between the intervention and placebo groups are used for safety analyses. All tests of significance will be at the 5% significance level and two-sided. All of the data in this trial will be assessed with SPSS Statistics version 20.0 (SPSS, Chicago, Illinois, United States). The main analysis will be fully specified before unmasking.

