Side effects	Headache, dizziness, nausea, and drowsiness, determined daily by physical examination by the intensivist, and withdrawal symptoms upon discontinuation evaluated after the drugs are stopped.

NREM, None rapid eye movement; SWS, Slow wave sleep; REM, Rapid eye movement; PSG, Polysomnography; RCSQ, Richards Campbell sleep questionnaire; VAS-A, Visual analogue scale-anxiety; CAM-ICU, The confusion assessment method for the intensive care unit.

The primary outcome will be to determine the effect of melatonin administration on the 24-hour sleep-wake cycle and subjective sleep quality, including night/day sleep time, total sleep time(TST), percentages of NREM stage 1/2, slow wave sleep(SWS) and REM, the incidence of arousals per hour, the duration of sleep without waking and the number of sleep periods.

The secondary outcomes will be: (a) objective sleep quality as assessed by the Richards Campbell Sleep Questionnaire (RCSQ); (b) anxiety levels measured using the Visual Analogue Scale-Anxiety (VAS-A); (c) stress levels via measuring the plasma melatonin, cortisone and norepinephrine; (d) levels of oxidative stress; (e) levels of inflammation; (f) the number of delirium-free days in 8 and 28 days; (g) the number of ventilator-free days in 28 days; (h) the number of antibiotic-free days in 8 and 28 days; (i) ICU length of stay; (j) overall ICU mortality at 28 days; (k) the incidence and severity of melatonin side effects in ICU patients.

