### Randomization with double-blind and allocation concealment

The study has a prospective, randomized, double-blind, placebo-controlled, parallel-group design. Eligible patients are randomly assigned to one of the two treatment study groups, labelled the ‘melatonin group’ or the ‘placebo group’. Randomization is based on a computer-generated random digits table and follows a concealed process using sealed and numbered envelopes that allocate the patient to either of the two arms of the study. Patients may be randomized into this study only once, unless they were discharged from the hospital and were re-admitted more than 180 days after their first enrolment. The study does not allow crossover, and if any occur, they will be reported as protocol violations.

The experimental drug and a placebo with the same characteristics are prepared by a pharmacist. The patients and all study personnel except the investigative pharmacist are blinded to the treatment assignment. The details of the treatment assignments are unknown to any of the investigators and are contained in a set of opaque and sealed envelopes, each marked with only the randomization number.

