### Trial interventions

All patients are randomized at a ratio of 1:1 to the oral melatonin or placebo group. Time zero (T0) is defined by randomization and the study treatment and relevant inspections are started just after. The baseline data about the sleeping state of the patients needs to be recorded on day 1 after enrolment, thus the intervention begins on day 2. The melatonin group patients receive 3 mg of melatonin orally or through a feeding tube at 9:00 pm for four consecutive nights (from day 2 to 5) once they have enrolled in the study. If melatonin is administered by a nasogastric (or nasojejunal) tube, the tablet should be crushed and mixed with 20 ml of water, followed by another 20 ml to flush out the remnants inside the tube. The placebo group patients will receive the placebo orally or through a tube using identical methods and at the same time as the patients in the melatonin group.

After randomization, given the possible powerful effect of the high level of noise, turning on of the lights, or the intensive routine care and procedures on patients’ sleep in the ICU, we will offer earplugs and eye masks to the patients and we will dim the main light at night (from 9:00 pm to 7:00 am). Meanwhile, meetings and posters were employed to encourage staff to minimise environmental, nursing and clinical disturbances, such as clustering patient care activities during the nocturnal study periods. Additionally, nurses should select time periods to promote sleep by avoiding routine ICU care activities (such as the daily bath), reducing ambient noise and turning down the lights during these periods. Other therapy and nursing projects should follow the clinical guidelines and nursing criterion.

In particular, during the sleep evaluation and intervention period (T0 time - 9:00 pm on day 6), pain, delirium and agitation will be managed in accordance with local guidelines. In case of clinical indication for analgesia and sedation, which can influence the effectiveness of melatonin and sleep structure, the study treatment is stopped and the necessary related administration is started according to the decision of the investigators. To help manage complex cases, three flowcharts are proposed for pain, sedation and delirium (Figures 
1,
2 and

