### Data collection and management

Trained staff will record data and fill in the web-based collection forms. At the moment of patient inclusion, patient data on demographic characteristics and the history of past illnesses will be collected: age, sex, height and weight, Acute Physiology and Chronic Health Evaluation II(APACHE II) score, Sequential organ failure assessment(SOFA) score, Glasgow coma scale(GCS) score, diagnosis, and comorbidities. Clinical, physiological and analytical variables such as vital signs (temperature (T), blood pressure (BP), heart rate (HR), and respiratory rate (RR)), routine ICU laboratory tests (white blood count (WBC), serum creatinine (SCr), blood urea nitrogen (BUN), alanine aminotransferase (ALT), and aspartate aminotransferase (AST)) will be recorded at the moment of inclusion. The duration of time of ventilation, ventilation mode, the number of days in delirium, the ICU length of stay and the names, dose, duration of use and time of last use of sedatives, analgesics medications and vasopressor drugs will also be recorded prior to study inclusion.

Furthermore, sleep-related baseline data, including objective and subjective sleep quality and anxiety levels should be recorded. Subjective sleep quality, including the TST, the length of sleep at night (9:00 pm to 7:00 am) and in the day (7:00 to 9:00 pm), sleep architecture (NREM stage 1 and 2, SWS and REM), sleep disruption (the number of arousals and the duration of sleep), will be monitored for one 24-hour period using a portable PSG device from day 1 9:00 pm to day 2 9:00 pm. The PSG remains the gold standard for sleep quality assessment. Electroencephalographs (EEG; O1/M2, C4/M1), electromyographs (EMG), electrooculographs (EOG; right and left) and electrocardiographs (ECG; lead II) will be recorded. The patients’ skin will be prepared according to standard techniques. Gold cup EEG electrodes will be placed at O1/M2 and C4/M1 according to the International 10 to 20 System. Two EOG electrodes will be used for the right and left eye movements. The EMG electrodes will be located over the right and left masseter (facial) muscles. The electrode application will be performed by the specialist.

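### The intention-to-treat rule covers every analysis, so patients who never received study drug enter the side-effect comparison and shrink any difference between arms.

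*Protocol article*

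**What the plan says.** The Statistical analysis section of the protocol article opens with a rule that has no qualification: "All analyses will be performed according to the intention-to-treat principle, that is, all randomized patients will be analysed" in the groups to which they were allocated. Later in the same section the safety analysis is described in one sentence: "The differences in adverse events between the intervention and placebo groups are used for safety analyses". No separate population and no event window are given for it.

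The timing comes from two other sections.

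- Trial interventions sets the clock: "Time zero (T0) is defined by randomization and the study treatment and relevant inspections are started just after". It then explains that baseline sleep is recorded on day 1, "thus the intervention begins on day 2", with doses given "at 9:00 pm for four consecutive nights (from day 2 to 5".
- Data collection and management places the baseline polysomnography in the gap: sleep "will be monitored for one 24-hour period using a portable PSG device from day 1 9:00 pm to day 2 9:00 pm".

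The side effects are defined in Table 1: "Headache, dizziness, nausea, and drowsiness, determined daily by physical examination by the intensivist", together with withdrawal symptoms after the drug is stopped. The day on which daily recording starts is not stated.

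Three further passages bear on who is in the set. Trial interventions lets study treatment be stopped for analgesia or sedation at any time from T0. End of participation in the study lists refusal, a new exclusion criterion, a severe adverse event, worsening, discharge and death. Ethical aspects and informed consent says that patients who withdraw are followed clinically but their data are not analysed.

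**The concern.** Intention to treat is the right default for efficacy, where including untreated patients is the cautious choice. For harm the same dilution works the other way: it makes a drug that causes side effects look closer to placebo.

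This design leaves room for the problem. Every patient has a drug-free period of at least 24 hours after randomisation, and the article itself provides ways to stop or leave during it. Some randomised patients may therefore never take study drug. Safety is half of the stated objective, and side effects are a listed secondary outcome. A later analysis plan that defined a dosed safety set would contradict the sentence as it stands, so this is a stated rule and not merely a detail left for later.

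**Working it through.** The article gives no safety figure to reproduce: no expected side-effect rate and no never-dosed share. The check is therefore of direction, followed by an illustration on assumed inputs.

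**Time from randomisation to first dose.** Baseline polysomnography starts at 9:00 pm on day 1 and the first dose is at 9:00 pm on day 2. If randomisation falls on day 1 between midnight and 9:00 pm, the gap is 24 to 45 hours. From the first dose to 9:00 pm on day 6 is 4 × 24 = 96 hours.

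**Inputs**

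- From the article: 99 patients per arm, two-sided 5% level.
- Assumed: 96-hour risk of any side effect p0 = 20% on placebo and p1 = 35% on melatonin among dosed patients; share never dosed f = 5%, 10% or 15% in each arm; never-dosed patients carry the placebo risk.

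**Step 1. What the stated rule does.** The placebo-arm risk stays at p0. The melatonin-arm risk becomes q = p0 + (1 − f)(p1 − p0), so the risk difference shrinks by the factor (1 − f). Without dilution the difference is 15 points and the risk ratio 0.35/0.20 = 1.75. Power is from the normal approximation for two proportions.

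| f | q | Difference (points) | Risk ratio | Power, all randomised (99 per arm) | Power, dosed only (n per arm) |
|---|---|---|---|---|---|
| 5% | 0.2 + 0.95 × 0.15 = 0.3425 | 14.25 | 1.71 | 62% | 64% (94) |
| 10% | 0.2 + 0.90 × 0.15 = 0.335 | 13.5 | 1.68 | 57% | 61% (89) |
| 15% | 0.2 + 0.85 × 0.15 = 0.3275 | 12.75 | 1.64 | 53% | 59% (84) |

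The all-randomised analysis loses about 2, 4 and 6 points of power against the dosed-only one, even though the dosed-only set is smaller.

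**Step 2. What would follow if side effects were also counted from randomisation.** The article does not say this, so the step is conditional. Take constant hazards h = −ln(1 − p)/96, which gives 0.00232 per hour on placebo and 0.00449 on melatonin. With a pre-dose time t of 24 or 45 hours, the placebo-arm risk is 1 − exp(−h0(t + 96)) = 24.3% or 27.9%. Dosed melatonin patients have risk 1 − exp(−(h0·t + h1·96)) = 38.5% or 41.5%, and never-dosed patients have the placebo-arm risk. At f = 10%:

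- t = 24: melatonin arm 0.9 × 38.5% + 0.1 × 24.3% = 37.1%; risk ratio 1.52; power 49%.
- t = 45: melatonin arm 0.9 × 41.5% + 0.1 × 27.9% = 40.1%; risk ratio 1.44; power 44%.

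Across f = 5% to 15% and both values of t, the risk ratio lies between 1.55 and 1.41. Most of this further loss comes from the pre-dose window. With nobody undosed, the window alone gives 1.58 to 1.48.

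**Sensitivity to the assumed risks.** With 10% on placebo and 25% on melatonin, 10% never dosed takes the risk ratio from 2.50 to 2.35. Power is 72%, against 75% in a dosed-only set. The direction and the modest size of Step 1 do not depend on the particular pair of rates.

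**The case against.** The strongest reply is that little of the possible damage is actually written down. Intention to treat fixes a population and an allocation rule; it does not require events to be counted from randomisation. A reader might infer from T0, and from inspections starting just after it, that pre-dose symptoms will be counted as melatonin side effects. The article does not support that: the inspections are not named, and Table 1 gives no start day for the daily examination. This part of the reply stands, and it removes most of the larger figures.

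A reader might also infer that the rule understates side-effect incidence under melatonin in every case. It does not. Never-dosed patients add to the denominator and lower the arm's rate, but pre-dose events, if counted, raise it in both arms: to 37% to 40% on melatonin in Step 2, against 35% among dosed patients. Only the attenuation of the contrast is common to both mechanisms.

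Other parts of the reply also carry weight. Candidates must be clinically stable and off sedation for 36 to 48 hours, so the never-dosed share may be small. The consent section removes withdrawn patients, some of whom would be never dosed, although that in turn conflicts with analysing all randomised patients. Product mix-ups should be rare in a pharmacist-prepared, concealed scheme; the article says "The study does not allow crossover, and if any occur, they will be reported as protocol violations". An as-randomised harm table is a legitimate display in a blinded trial.

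What does not stand is that the matter is simply left to the analysis plan. The article states a rule for all analyses, and that rule reaches safety.

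**Conclusion.** The point holds in a limited form. As written, the intention-to-treat sentence governs the adverse-event comparison. Given a first dose at least 24 hours after randomisation, it admits patients who never took study drug and biases the comparison toward no difference.

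The direction follows from the article, provided that some analysed patients are never dosed and that melatonin does raise the risk. The size does not. On assumed risks of 20% and 35% with 5% to 15% never dosed, the risk ratio falls from 1.75 to 1.71–1.64, and power is about 2 to 6 points below a dosed-only analysis. The range 1.55 to 1.41 applies only if events are counted from randomisation, which the article leaves open. This is a worthwhile, inexpensive improvement and not a flaw that threatens the trial.

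**What to change.** In Statistical analysis, limit the intention-to-treat sentence to efficacy and mortality. Add that side effects are analysed in patients who received at least one dose, grouped by the product received, counting events that start or worsen after the first dose. Keep the all-randomised table as supporting information.

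In the same edit, reconcile the sentence with Ethical aspects and informed consent, so that it is clear whether the data of withdrawn patients are used and for which analyses.

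The cost is one or two sentences and one extra table, settled before unmasking. The downside is a slightly smaller safety set that is not strictly as randomised. Because treatment is blinded, exclusion before the first dose should introduce little bias.

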The sound and illuminance levels are recorded from day 1 to day 6 using the integrated sound pressure level meter and the illuminance level meter. Continuous equivalent sound pressure levels (Leq) in ‘A’ weighted decibels and peak sound pressure levels (Lpeak) in ‘C’ weighted decibels are logged every second. The illuminance level (in lux) is recorded once per minute using a sensor placed close to the patient’s head. The bedside nurse should be asked to log an event whenever the patient received treatment or care. The event log will contain the following items: clinical assessment, tracheal suctioning, pressure area care, physiotherapy, mouth or eye care, blood test (sampling), washing, non-invasive blood pressure, eating and drinking, dressing, pain, line insertion and X-ray. Drug records are compiled daily for drugs that are known to adversely affect sleep or melatonin pharmacokinetics.

At the time of the ICU discharge, patients’ data and vital statuses, lengths of mechanical ventilation, the number of days of antibiotics use, the number of delirium-free days, the length of the ICU stay and ICU mortality will be recorded.

To investigate the enteral absorption and metabolism of orally administered melatonin in critically ill patients during their ICU stay and to evaluate the serum melatonin levels and their circadian variations in these patients, the melatonin levels are measured in blood samples taken on days 1 and 2 (before the intervention) and days 5 and 6 (four days after the intervention) at 20:45 (before administration), 9:10 pm, 9:30 pm, 00:00 am, 3:00 am, 6:00 am, 2:00 pm and 8:00 pm in 20 patients from each group. The plasma levels of norepinephrine and cortisol are also measured at the same time points. In addition, plasma levels of SOD, MDA, catalase (CAT), IL-6 and IL-8 are measured at 07:00 am on days 2 and 6.

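### For the five oxidative-stress and inflammation markers the plan permits adjustment for the pre-dose value but does not commit to it, and an unadjusted day-6 comparison would be valid but less efficient

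*Protocol article*

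**What the plan says.** The protocol article's outcome list (Study design and outcomes) includes "d) levels of oxidative stress; (e) levels of inflammation" among the secondary outcomes. Under Data collection and management, "plasma levels of SOD, MDA, catalase (CAT), IL-6 and IL-8 are measured at 07:00 am on days 2 and 6". Under Trial interventions, the study drug is given "at 9:00 pm for four consecutive nights (from day 2 to 5". The day-2 sample therefore comes 14 hours before the first dose, and the day-6 sample 10 hours after the last.

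The Statistical analysis section has three statements that could govern these markers:

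- The general rule: "Comparisons of continuous variables will be performed using Student’s" t-test when normally distributed, and Mann-Whitney otherwise.
- The sentence straight after it: "regression will be generated for the identification of the determinants of outcomes and for the correction of baseline covariates". It names neither the covariates nor the outcomes.
- The repeated-measures ANOVA sentence, which covers "the sleep variables, the subjective sleep quality, anxiety levels and plasma levels of melatonin, cortisol and norepinephrine". The five markers are not in that list.

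**The concern.** Each marker has a true pre-dose value, collected by design, in every patient who is sampled. The plan gives melatonin, cortisol and norepinephrine a method that uses the repeated measurements. For these five markers it names only two-sample tests, which take no covariate.

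If those tests are run on day-6 values alone, stable differences between patients stay in the error term although the data to remove part of them are in hand. Two named secondary outcomes would then be tested with less power than the same samples allow. A Mann-Whitney result would also come without an adjusted effect estimate. Finally, because the text allows both a simple test and a regression without ranking them, the result to be reported as the main one is not fixed.

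**Working it through.** **1. Which rule applies.** The ANOVA sentence lists its variables and omits SOD, MDA, CAT, IL-6 and IL-8. No other sentence names them. They therefore fall to the t-test/Mann-Whitney rule, with the regression sentence as an unspecified addition.

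**2. The plan's own figure.** The article gives no power figure for these markers. Its only one is 82 evaluable patients per arm for night sleep (Current sample size justification). With the stated 0.7 h difference and SD 1.8 h, a two-sided two-sample calculation at 5% and 80% power gives 104 per arm; 82 comes out only one-sided. That is a separate matter. Here 82 serves only as an illustrative sample size, and the power results in step 4 do not depend on it.

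**3. Inputs and formulas.** From the article: "All tests of significance will be at the 5% significance level and two-sided", and 1:1 allocation. Assumed: the correlation rho between day-2 and day-6 values, which the documents do not give; equal SDs at the two times; and a linear relation on the analysis scale.

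- Standardised effect that a day-6-only t-test detects with 80% power: d = (1.960 + 0.842) × √(2/n). With n = 82 per arm, d = 0.438.
- Variance of the baseline-adjusted effect relative to day-6-only: 1 − rho².
- Variance of a change-score comparison relative to day-6-only: 2(1 − rho).
- Power at d under relative variance f: Φ(2.802/√f − 1.960).

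**4. Results at the effect where the day-6-only test has 80% power.**

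| rho | 1 − rho² | Power, adjusted | n per arm for 80%, adjusted | Power, change score |
|---|---|---|---|---|
| 0 | 1.00 | 80.0% | 82 | 50.8% |
| 0.2 | 0.96 | 81.6% | 79 | 60.1% |
| 0.3 | 0.91 | 83.6% | 75 | 65.8% |
| 0.5 | 0.75 | 89.9% | 62 | 80.0% |
| 0.7 | 0.51 | 97.5% | 42 | 95.1% |

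Example at rho = 0.5: 2.802/√0.75 = 3.235; 3.235 − 1.960 = 1.275; Φ(1.275) = 0.899.

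**5. Effect of the number sampled.** Data collection and management restricts the serial melatonin samples to 20 patients per group. It does not say clearly whether the five markers follow that subset or are taken in everyone. At rho = 0.5 the detectable difference shrinks by the factor √0.75 = 0.866 in either case: from 0.438 to 0.379 SD with 82 per arm, or from 0.886 to 0.767 SD with 20 per group (normal approximation). The proportional gain is the same, but the absolute sensitivity is very different.

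**6. What is not computed.** The table compares a t-test with a linear model under normality. The loss on the Mann-Whitney route depends on the marker distributions, which the documents do not describe.

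**The case against.** The strongest reply is that the regression sentence already covers this. A pre-dose marker level is a natural baseline covariate, and nothing in the text excludes it. That stands. A reader might infer that the plan discards the day-2 value, or leaves chance baseline imbalance uncorrected. The documents do not support either statement; they show only that using the value is allowed and not promised.

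Second, the text does not say whether the simple test is applied to day-6 values or to changes from day 2. A change score would use the pre-dose value, so it also goes too far to say that the named tests necessarily ignore it. This stands as well, but it does not rescue efficiency: a change score beats the day-6-only test only when rho exceeds 0.5. The adjusted model is at least as efficient at any rho, because 1 − rho² = (1 − rho)(1 + rho) never exceeds 2(1 − rho).

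Third, naming covariates for secondary biomarkers often belongs in a statistical analysis plan, and the article says that the main analysis will be fully specified before unmasking. Merely missing detail would not be a point. However, the article does state a test for continuous variables and does list which variables get something else. The suggestion is to replace that stated rule, for these markers, with a more efficient one.

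Fourth, an unadjusted comparison of randomised arms is valid, and no power is claimed for these outcomes. Both are true, and they keep the point small.

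**Conclusion.** The point holds as a low-cost improvement and not as an error. The plan collects a pre-dose value for all five markers, names only unadjusted two-sample tests for comparing the arms, and permits adjustment in general terms without committing to the day-2 value or ranking the adjusted result first.

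If the analysis proceeds on day-6 values alone, the cost is efficiency only. Relative to 80% power, 1.6 points are forgone at rho = 0.2, 3.6 at 0.3, 9.9 at 0.5 and 17.5 at 0.7, and none at rho = 0. These figures rest entirely on an assumed correlation, on equal SDs and on approximate normality on the analysis scale. The number of patients sampled is unclear, which affects the absolute detectable difference but not these gains. No bias is shown, and the primary outcome is not affected.

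**What to change.** In the Statistical analysis section, add one sentence for SOD, MDA, CAT, IL-6 and IL-8. The main between-arm comparison is a linear model of the day-6 value on treatment and the day-2 value of the same marker, both log-transformed if the marker is skewed. Report the adjusted difference, or the adjusted ratio of geometric means, with its 95% confidence interval. The t-test or Mann-Whitney test can stay as a supporting analysis.

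The cost is one sentence, written before unmasking. It uses samples that are already planned and needs no additional patients or assays. The only statistical price is one degree of freedom per model, which is negligible even with 20 per group.

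### The test named for the sleep, anxiety and hormone outcomes, a one-way repeated-measures ANOVA, has no arm term, so the text conflicts on the primary between-arm comparison

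*Protocol article*

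**What the plan says.** In the protocol article, the second paragraph of Statistical analysis gives the sleep outcomes their own test: "One-way repeated measures analysis of variance (ANOVA) were used to determine differences in the sleep variables". The sentence goes on to cover "the subjective sleep quality, anxiety levels and plasma levels of melatonin, cortisol and norepinephrine". It names no arm factor and no arm-by-time term.

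The paragraph before it has two general sentences. "Comparisons of continuous variables will be performed using" Student's t-test or the Mann-Whitney U test, depending on normality. Linear, logistic or Poisson "regression will be generated for the identification of the determinants of outcomes and for the correction of baseline covariates". Neither names an outcome.

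Current sample size justification states a between-arm null hypothesis (equal means in the experimental and control groups) and a between-arm difference of 0.7 h in nightly sleep.

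Data collection and management schedules a baseline PSG that "will be monitored for one 24-hour period using a portable PSG device from day 1 9:00 pm to day 2 9:00 pm", before the first dose, and a second 24-hour PSG from day 5 to day 6. RCSQ and VAS-A are likewise taken once at baseline (day 2) and once after treatment (day 6). The same section confines the analyses to the fourth treatment day.

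**The concern.** A one-way repeated-measures ANOVA asks whether the mean differs between measurement times. The trial asks whether melatonin differs from placebo. Sleep is the primary outcome domain, and the only sentence that assigns it a test assigns one that cannot answer that question. By contrast, the delirium-free, ventilation-free and antibiotic-free days get an explicit two-group test.

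A change over time common to both arms could then be reported as a significant difference in sleep. Separately, a pre-treatment PSG is scheduled for every patient, yet the text does not commit to using it in the main comparison.

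**Working it through.** **1. Inputs from the protocol article.** Nightly sleep mean 3.5 h, SD 1.8 h, between-arm difference 0.7 h, power 0.8, two-sided alpha 0.05, 82 per arm before dropout and 99 recruited per arm with 20% dropout (Current sample size justification). Evaluable per arm: 99 × 0.8 = 79.2, taken as 79.

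**2. The plan's own figure.** For two independent means, n = 2 × [SD × (z_alpha + z_power) / difference]².
- Two-sided: 2 × [1.8 × (1.960 + 0.842) / 0.7]² = 103.8, so 104 per arm.
- One-sided: 2 × [1.8 × (1.645 + 0.842) / 0.7]² = 81.8, so 82 per arm.

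The stated 82 is reproduced only one-sided. That is a separate sample-size point. It matters here because the unadjusted two-sided comparison falls short of 80% power at the planned size.

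**3. What the named test does with these data.** With one baseline and one day 5-6 value, a one-way repeated-measures ANOVA is a paired t-test on the change, with F = t². Arm does not enter.

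**4. Rejection rate with zero drug effect and a shared gain g in both arms.** SD of change = 1.8 × √(2(1 − ρ)), where ρ is the baseline to day 5-6 correlation. Noncentrality = g × √n / SD of change, with n = 158 pooled or 79 within the melatonin arm. Both g and ρ are assumptions. Rates are from the noncentral t distribution, two-sided 5%.

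| ρ | SD of change (h) | g = 0.25 h: pooled / melatonin arm | g = 0.5 h: pooled / melatonin arm |
|---|---|---|---|
| 0.3 | 2.130 | 31% / 18% | 84% / 54% |
| 0.5 | 1.800 | 41% / 23% | 93% / 68% |
| 0.7 | 1.394 | 61% / 35% | 99% / 88% |

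Example: ρ = 0.5, g = 0.5, pooled: 0.5 × √158 / 1.8 = 3.49. In simulation, a between-arm t-test on the post-treatment value stays at about 5% whatever the shared gain.

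**5. Power for a true 0.7 h difference at 79 per arm.** Noncentrality = 0.7 × √(79/2) / SD used.
- Unadjusted t-test, SD 1.8: 2.44, power 68%.
- ANCOVA, SD = 1.8 × √(1 − ρ²): 1.717, 1.559 and 1.285 at ρ = 0.3, 0.5 and 0.7; power 72%, 80% and 93%.

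**6. If a two-factor (arm by time) ANOVA was meant.** The interaction uses the SD of change in the table: power 54%, 68% and 88% at ρ = 0.3, 0.5 and 0.7. The arm main effect averages baseline and follow-up, so the effect halves to 0.35 h with SD = 1.8 × √((1 + ρ)/2) = 1.451, 1.559 and 1.660: power 33%, 29% and 26%. The reading matters, and the text does not settle it.

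**The case against.** The strongest reply is that an arm comparison is already in the document. The null hypothesis is between arms, patients are analysed as allocated, night sleep time is continuous, and the generic t-test/Mann-Whitney sentence does not exclude it. Restricting analysis to the fourth day also points to a single post-treatment comparison. This stands in part. A reader might infer that the plan has no between-arm test at all, and the documents do not support that. But the specific sentence sends these outcomes elsewhere, so the text conflicts.

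A reader might add the paired t-test in the sample-size section as a third competing analysis. It is a label on the sizing calculation, attached to a between-group null, and not an analysis commitment.

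The rates in step 4 might be read as false-positive rates for melatonin. They are rejection rates for a time change that the calculation assumes. They become false drug claims only if a time effect is reported as a treatment effect.

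Earplugs, eye masks and dimmed light might seem a sure source of such a change. They are introduced after randomization, and the baseline PSG is also recorded after randomization, so they may already be in place at baseline. Enrolled patients are required to be stable, so recovery over four days is also only an inference.

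For the hormones, serial sampling in 20 patients per group is meant partly to describe circadian variation, and a time factor suits that. Stress hormone levels are also a secondary outcome of a two-arm trial, so an arm term is still needed.

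Finally, the article is condensed and says that the main analysis will be fully specified before unmasking. That leaves room to correct the sentence but does not make the stated test right. ANCOVA and dropping the Kolmogorov-Smirnov check are not needed for validity: an unadjusted t-test holds its 5% error.

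**Conclusion.** The point holds as a conflict over the primary comparison. The one test named for the sleep variables, RCSQ, VAS-A and hormones does not, as written, test melatonin against placebo. The sentences that could do so are not tied to these outcomes. This should be corrected before unblinding because it concerns the primary domain.

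The consequence depends on a shared change over time. For assumed gains of 0.25 to 0.5 h and correlations of 0.3 to 0.7, the named test is significant without a drug effect in 31-99% of trials pooled and 18-88% within the melatonin arm. With no shared change it stays near 5%. The documents give neither the gain nor the correlation, so these figures show how exposed the test is and do not predict what will happen.

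The power gain from ANCOVA is a further benefit that rests on the same unknown correlation: 4 points at 0.3, 12 at 0.5 and 25 at 0.7, from a base of 68%.

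**What to change.** Replace the sentence before unblinding.
- **Primary:** ANCOVA of day 5-6 night sleep time on arm, adjusted for the same PSG variable from day 1-2, reporting the adjusted mean difference with its 95% confidence interval.
- **Other PSG variables, RCSQ and VAS-A:** the same model, each with its own baseline.
- **Serial plasma melatonin, cortisol and norepinephrine:** a mixed model with arm, time and arm-by-time.
- **General sentences:** say that the t-test/Mann-Whitney and regression sentences do not govern these outcomes.

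The baseline measurements are already scheduled ("sleep-related baseline data, including objective and subjective sleep quality and anxiety levels should be recorded"), so no patients or assessments are added and the cost is analysis wording. It should not be justified by saying that all data are in hand: Trial status describes a trial still running, with one interim analysis done. Record the change as made after that interim analysis and before unmasking.
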